**Figure 4 figure4:**
[figure not shown]
Adapted Theoretical Framework of Acceptability Questionnaire.

#### Data Analysis

Objectives 1, 2, and 4 will be evaluated descriptively via bar graphs, means, and SDs to compare each objective across administration settings and VR stage according to preset feasibility criteria. Preset feasibility criteria must be met to determine if the VR program is acceptable (mean Theoretical Framework of Acceptability Questionnaire score >3, which indicates a more favorable acceptability rating than no opinion; Sekhon et al [54]), tolerable (at least 70% of the participants do not report any pre- or post-NRS score increases of ≥3 for PLP, RLP, or nausea), and engaging (mean session duration ≥20 min). Similar progression criteria [52] must be met to determine whether procedural feasibility is appropriate for an RCT, including recruitment (at least 50% of the patients at the HSC who appear to meet the eligibility criteria will be screened through the established pathways), retention (at least 70% of the participants who live in Winnipeg will continue to participate in the study for as long as they are able to), and attrition (at least 80% of the participants will respond at the 1-month follow-up period following their final session) rate criteria. The sample will also be compared to the population of all people who underwent an LLA at the HSC during the recruitment period (from June 2024 to March 2025) via administrative chart review to evaluate whether the characteristics are relatively proportional to one another.

For objective 3, scatterplots will be generated to explore the association between the length of program engagement and the Brief Pain Inventory or Patient Reported Outcomes Measurement Information System pain interference. Mean or median difference in length of program engagement between participants who have and have not yet experienced PLP onset will also be calculated. If appropriate, exploratory regression models will be used to examine the effect of VR dosage on PLP outcomes.

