#### VR Intervention Procedure

Participants engaged in 1 VR session per day for approximately 20 minutes from their respective ward (orthopedic, vascular, or rehabilitation). At the beginning of the first VR session, after informed consent was obtained and the honorarium was given to the participant, the research assistant administered the sociodemographic and patient characteristic questionnaire (including age, amputation etiology, place of residence, etc). The research assistant then gave a brief verbal introduction to the VR-GMI system and instructed the participant on how to use the VR headset and handheld controls. Following VR instruction and at the beginning of each subsequent VR session, the research assistant verbally administered the Numerical Rating Scales (NRSs; 11-point Likert scales) for PLP, residual limb pain (RLP; ie, physical pain at the amputation site), and nausea before asking if they wanted to engage with the VR program that day. If they declined participation, their reason was recorded.

Participants were only permitted to engage in 1 stage per day. They could only move onto the next VR stage if their RLP, PLP, or nausea NRS scores did not increase by >2 points during or before their next session (given that treatment may exacerbate pain or nausea, and 3 points is considered a clinically significant increase) [44-47]. The participants were permitted to spend as much time as they preferred in each VR stage. If the participant chose to stop the session before the 20-minute goal (a session length used in previous studies) [23,48], the research assistant asked for and recorded their reason for discontinuation. Afterward, the research assistant verbally readministered the NRSs for PLP, RLP, and nausea. Any impromptu feedback or observations made by research personnel were recorded as field notes.

Participants were asked to engage in up to 10 VR-GMI sessions or until hospital discharge, whichever came first. After the last VR-GMI session, before discharge, the Igroup Presence Questionnaire (measuring VR immersion) [49] and VR Impressions Scale (developed by the laboratory for the purposes of descriptive evaluation of a VR intervention; Figure 3) [50] were administered.

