#### Recruitment

The research team aims to recruit 30 participants, 5 (17%) of whom we expect to drop out and 25 (83%) to complete the program. This sample size is in line with previous pilot studies for PLP treatments that precede RCTs [38] and suits the descriptive and exploratory aims of the study. This sample size also has 80% power to detect the desired recruitment criterion [53].

Potential participants will be approached according to the recruitment strategies and eligibility criteria outlined and recommended in phase 3, with 3 exceptions to help mitigate recruitment barriers faced in the previous phase. First, clinical resource nurses on units where LLAs are treated at the HSC will be called each week to ascertain where eligible patients are to increase the recruitment rate. Second, individuals with bilateral amputations will also be eligible for recruitment, given preliminary data from phase 3 suggesting this may be feasible. Third, patients will be eligible to participate for up to 2 months following their LLA, in line with the literature that suggests such a time frame is suitable for the administration of acute PLP intervention [20].

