#### VR Intervention Procedures

Similar procedures to phase 3 will be used in phase 4A, with 3 exceptions made in accordance with preliminary phase 3 data. First, following baseline measure administration, the research assistant will administer a brief video via laptop that introduces the participant to the VR-GMI program, including how to operate the controls and put on the headset. The video (rather than verbal instruction) serves to standardize study expectations and technical knowledge across participants. Second, new measures have been introduced in addition to the measures used in phase 3. The first time a participant completes a stage, they will be administered the Theoretical Framework of Acceptability Questionnaire, which consists of 7 items rated on a 7-point Likert scale inquiring about the acceptability of a behavioral intervention [54] (Figure 4). In addition, following the limb simulation stage (both with and without leg tracking), each participant will be administered the Virtual Embodiment Questionnaire, a validated measure for agency and ownership in a virtual experience involving avatar embodiment [55]. Finally, the Brief Pain Inventory and Patient Reported Outcomes Measurement Information System will be verbally administered over the phone 1 month following each participant’s final VR session to measure PLP intensity and interference, respectively, through validated self-report measures [56-58].

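### The acceptability criterion of a mean above 3 fits the stated 7-point scale only if items are coded 0–6; under the usual 1–7 coding it lies one point below neutral

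*Protocol article*

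**What the plan says.** Two sections of the protocol article bear on this, both under Phase 4A.

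- *VR Intervention Procedures* introduces the acceptability questionnaire, given the first time a participant completes each stage. It "consists of 7 items rated on a 7-point Likert scale inquiring about the acceptability of a behavioral intervention". The number of response points is given; the numeric codes and verbal anchors are not.
- *Data Analysis* sets the decision rule: "Preset feasibility criteria must be met to determine if the VR program is acceptable". For acceptability, the rule is a "mean Theoretical Framework of Acceptability Questionnaire score >3, which indicates a more favorable acceptability rating than no opinion".

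The form is reproduced as Figure 4, captioned "Adapted Theoretical Framework of Acceptability Questionnaire". The figure is not available in the text reviewed, so any codes or anchors printed on it could not be read.

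**The concern.** The criterion explains itself. A mean above 3 is meant to show that participants rate the program better than having no opinion, so 3 must be the neutral response. On a 7-point scale coded in the usual way, from 1 to 7, the neutral response is 4. A mean between 3 and 4 would then be on the unfavorable side of neutral, and the rule would read it as favorable.

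This is the only numerical rule for acceptability. Acceptability is one of three intervention criteria, with tolerability and engagement, and the Phase 4A overview says the data will be used to judge whether program and procedures are sufficient for a randomized trial. A threshold one point too low would let the program count as acceptable when its users were neutral or mildly negative.

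**Working it through.** **Inputs**

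- Threshold: mean above 3, with 3 as the neutral point (Phase 4A, Data Analysis).
- Response scale: 7 points, codes not stated in the visible text (Phase 4A, VR Intervention Procedures).
- Sample size: "The research team aims to recruit 30 participants, 5 (17%) of whom we expect to drop out and 25 (83%) to complete the program" (Phase 4A, Recruitment).
- SD of the score: not given. I assume 1.0 to 2.0, for illustration only.
- I also assume that the score is averaged over items, that higher is more favorable (as the criterion implies), and that each participant contributes one score.

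**Step 1. Can the stated neutral value of 3 be reproduced?**

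Midpoint = (lowest code + highest code) / 2.

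| Form and coding | Midpoint | Is 3 neutral? |
|---|---|---|
| 7 points, 1 to 7 | (1 + 7)/2 = 4 | No; 3 is one point below neutral |
| 7 points, 0 to 6 | (0 + 6)/2 = 3 | Yes |
| 7 points, −3 to +3 | (−3 + 3)/2 = 0 | No; a mean above 3 cannot occur |
| 5 points, 1 to 5 | (1 + 5)/2 = 3 | Yes, but the article says 7 points |

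The coding from −3 to +3 is ruled out, because no score could exceed 3. The article's figure is reproduced with 7 points coded 0–6, or with a 5-point form coded 1–5. It is not reproduced with 7 points coded 1–7.

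**Step 2. What passes under 1–7 coding?**

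Any mean above 3 passes, so means above 3 and up to 4 pass although they are not better than neutral. A concrete case: if 24 of 25 completers score 3 and one scores 4, the mean is (24 × 3 + 4)/25 = 76/25 = 3.04, and the program is declared acceptable.

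**Step 3. How often would this happen under 1–7 coding?**

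Normal approximation: P(sample mean > c) = Φ((μ − c)/(SD/√n)).

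For n = 25, SD/√n = SD/5. With μ = 3.5, c = 3 and SD = 1.5, this is Φ(0.5/0.3) = Φ(1.67) = 0.952. With c = 4 it is Φ(−1.67) = 0.048. The other cases follow in the same way:

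| n | SD | True mean | P(mean > 3) | P(mean > 4) |
|---|---|---|---|---|
| 25 | 1.0 | 3.5 | 0.994 | 0.006 |
| 25 | 1.5 | 3.5 | 0.952 | 0.048 |
| 25 | 2.0 | 3.5 | 0.894 | 0.106 |
| 30 | 1.5 | 3.5 | 0.966 | 0.034 |
| 25 | 1.0 | 4.0 | 1.000 | 0.500 |
| 25 | 1.5 | 4.0 | 1.000 | 0.500 |
| 25 | 2.0 | 4.0 | 0.994 | 0.500 |

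Under 1–7 coding, a program that users regard with exact neutrality would therefore pass more than 99% of the time. Under 0–6 coding these probabilities show no defect, because a true mean of 3.5 is then above neutral and ought to pass.

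**The case against.** The strongest reply is that the text contains no contradiction. It gives the number of response points and a neutral value of 3, and with unit steps and a central neutral response those two facts together imply 0–6 coding. Both sections are then correct as written. The article also describes other scales by their number of points alone: the pain and nausea ratings in Phase 3 appear as "Numerical Rating Scales (NRSs; 11-point Likert scales", again without codes. Silence about the codes is therefore not evidence of 1–7 coding, and Figure 4 may print them. This stands, and it is why the point is conditional.

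A reader might go further and infer that the threshold definitely sits below the midpoint, so that an unfavorably rated program would be declared acceptable, or that either the threshold or the scale description must be wrong. The documents do not support either inference. Under 0–6 coding neither statement is wrong. Even under 1–7 coding, only means above 3 and up to 4 are misread; means of 3 or below still fail.

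Two further replies limit the consequence. Progression also depends on tolerability, engagement, recruitment, retention and attrition criteria, with focus groups to follow and a further feasibility trial foreseen if significant adjustments are needed. And the probabilities rest on an assumed SD and one score per participant, whereas the questionnaire is given once per stage and results are compared across stages and settings. Both are fair. They reduce the weight of the point but do not settle which coding applies, and the acceptability rule must still be met in its own right.

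**Conclusion.** The point holds conditionally. The visible text states a decision threshold and its meaning but not the coding that would make them agree with a 7-point scale. Under 1–7 coding, neutral is 4 and the rule contradicts its stated rationale over the range above 3 and up to 4. With n = 25, a true mean of 3.5 and an assumed SD of 1.0 to 2.0, the chance of being declared acceptable would be about 99% to 89%, against 1% to 11% with a threshold of 4. Under 0–6 coding the threshold is correct and only the coding needs stating. With a 5-point form coded 1–5 the threshold is correct and the description of the scale is wrong. The documents at hand cannot show which case applies; the form actually used can.

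**What to change.** Take the numeric coding and the neutral anchor from the form given to participants, not from the scores collected, and state both beside the criterion in Phase 4A, Data Analysis. Then reconcile that section with VR Intervention Procedures before acceptability is judged:

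- 7 points coded 1–7: change the criterion to a mean above 4.
- 7 points coded 0–6: keep a mean above 3 and state the coding.
- 5 points coded 1–5: keep a mean above 3 and correct the description of the scale.

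The cost is about one line of text and no new data. The only downside arises under 1–7 coding, where the criterion becomes harder to meet. Fifteen participants had already been recruited by March 2025, so the correction should be documented as following from the form, to make clear that the threshold was not chosen with the results in view.

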The last and most significant amendment made between phases 3 and 4A is the administration of the VR-GMI program in the home setting following hospital discharge. Data from phase 3 suggested that participants were discharged from the hospital before 2 weeks had passed, which prevented them from receiving the VR dose necessary to see a treatment effect [23]. Therefore, a research assistant will contact participants over the phone following their discharge to inquire about their interest in continuing participation for the remaining sessions in their home. If they wish to continue (and they live in Winnipeg), their participation will proceed with home visits. If they do not reside in Winnipeg, their participation will be discontinued by the researcher; however, their willingness to continue the program will be recorded. Participants will be allowed to continue the VR-GMI program for up to 17 days to analyze long-term acceptability and dosage effects. Immediately following the completion of the feasibility trial, relevant modifications will be made to the prototype based on results.

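### The tolerability criterion counts any NRS rise over an exposure of one session to 17 days, so fewer sessions make it easier to pass; mean session duration has a related, conditional weakness

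*Protocol article*

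**What the plan says.** The phase 4A Data Analysis section sets preset criteria that have to be met before the program is called feasible. Two matter here.

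- Tolerability: "at least 70% of the participants do not report any pre- or post-NRS score increases of ≥3 for PLP, RLP, or nausea".
- Engagement: "engaging (mean session duration ≥20 min").

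Neither is tied to a number of sessions. Exposure is set elsewhere and varies:

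- Phase 4A VR Intervention Procedures: "Participants will be allowed to continue the VR-GMI program for up to 17 days".
- The same section, on discharge: "If they do not reside in Winnipeg, their participation will be discontinued by the researcher".
- That section also carries the phase 3 procedures forward ("Similar procedures to phase 3 will be used in phase 4A, with 3 exceptions"). None of the listed exceptions changes the NRS timing or the freedom to decline. Under the phase 3 VR Intervention Procedure there is one session a day. The pain and nausea scores are taken "before asking if they wanted to engage with the VR program that day", and on a refusal the rule is "If they declined participation, their reason was recorded".

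**The concern.** An ever/never outcome depends on how long people are observed. A participant discharged to a rural address after three sessions has three occasions on which a rise can be seen; one who completes the course has up to 17. Both enter the same 70% proportion with equal weight. Withdrawing or declining because of discomfort removes later occasions for a rise, and the rule does not count such a withdrawal or refusal as a failure in itself. Poor tolerability that shows as leaving, not as a 3-point score change, therefore helps the criterion.

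These criteria inform whether the program and procedures go forward to an RCT. A pass reached through short exposure would not carry over to a trial in which participants are meant to complete a full course. The criteria are also to be compared across settings and VR stages, where session counts will differ, so those comparisons share the problem.

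**Working it through.** The plan states no per-session rate and derives no figure from these two criteria, so there is nothing of its own to reproduce. The risks, correlations, stopping shares and durations below are assumptions.

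**1. Direction.** Let S(k) be the probability of no rise of 3 or more in k sessions. A further session can add a first event but cannot remove one, so S(k) never increases with k, whatever the event rate or correlation.

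**2. Size, independent sessions.** S(k) = (1 − q)^k with q = 0.05:

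- k = 3: 0.95^3 = 0.857
- k = 5: 0.774
- k = 10: 0.599
- k = 17: 0.418

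The risk that just gives 70% event-free is q = 1 − 0.7^(1/k): 11.2% for 3 sessions, 3.5% for 10 and 2.1% for 17.

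**3. Size, correlated sessions.** Pain and nausea cluster within people. Take a beta-binomial with mean q = 0.05 and within-person correlation ρ, with a = q(1/ρ − 1) and b = (1 − q)(1/ρ − 1). Then S(k) is the product over j = 0 to k − 1 of (b + j)/(a + b + j). For ρ = 0.1, a = 0.45 and b = 8.55, so S(3) = (8.55/9)(9.55/10)(10.55/11) = 0.870.

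| ρ | S(3) | S(7) | S(17) |
|---|---|---|---|
| 0 | 0.857 | 0.698 | 0.418 |
| 0.1 | 0.870 | 0.759 | 0.605 |
| 0.2 | 0.882 | 0.800 | 0.699 |
| 0.3 | 0.892 | 0.831 | 0.761 |

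**4. Effect of dropout on the verdict.** With the planned 30 participants, 70% is 21. Take q = 0.03 and independence, and let a share f stop after 3 sessions while the rest do 17. The event-free share is (1 − f)(0.97^17) + f(0.97^3) = (1 − f)(0.596) + f(0.913). The chance of at least 21 of 30 is binomial.

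| f | Event-free share | P(pass) |
|---|---|---|
| 0 | 0.596 | 0.165 |
| 0.17 | 0.650 | 0.356 |
| 0.30 | 0.691 | 0.546 |
| 0.50 | 0.754 | 0.819 |

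The per-session risk is the same in every row. Correlation would narrow the spread.

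**5. Engagement.** Suppose 15 participants have 17 sessions of 22 min and 15 have 3 sessions of 12 min.

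- Pooled over sessions held: (15×17×22 + 15×3×12)/(15×17 + 15×3) = 6150/300 = 20.5 min, a pass.
- Mean of participant means: (22 + 12)/2 = 17.0 min, a fail.

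If duration is unrelated to attendance, for example 21 min in every session, both methods give 21.0 min and there is no inflation. Stopping early within a session works the other way: if 20% of 22-min sessions are cut to 8 min, the mean is 0.8×22 + 0.2×8 = 19.2 min.

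**The case against.** The strongest reply has four parts.

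- **The article does not say that only attended sessions are scored.** A reader might infer this, but the averaging unit and the handling of declined days are not stated and may be in a fuller document. The NRS is taken before the participant accepts or declines, so a score exists on declined days, and the wording leaves open whether between-session rises count. This stands. It does not rescue the tolerability rule, whose dependence on exposure follows from the text as published.
- **Stopping early does not always help.** A reader might infer that it eases both criteria. Ending a session early shortens the recorded duration and makes engagement harder to pass, and the repeat NRS is described directly after the early-stop provision. Nor can one person pass engagement by doing one long session and refusing the rest, because it is a group mean. Both points stand.
- **Independence exaggerates the effect.** This stands. The fall at 17 sessions is much smaller with plausible correlation, and a switch from pass to fail at about 7 sessions disappears: at 7 sessions the share is 76-83% for ρ of 0.1-0.3.
- **Uptake is handled elsewhere.** This stands only in part. The retention criterion covers Winnipeg residents alone, for as long as they are able. Reasons for session or study withdrawal are exploratory, without a threshold. Single declined sessions enter no criterion.

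**Conclusion.** The point holds for tolerability. The rule becomes easier to meet as exposure falls, and it does not treat leaving or declining because of pain or nausea as a failure. The direction is certain; the size is not. At an assumed mean per-session risk of 5%, the event-free share moves from about 86-89% at 3 sessions to 42% at 17 under independence, or to 60-76% with correlation of 0.1-0.3.

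For engagement the point is conditional. A mean pooled over sessions held omits declined days and gives most weight to those with many sessions, so it is inflated if low engagers attend fewer sessions, and not otherwise.

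A reader might go further and conclude that the criteria measure length of stay and residence instead of the program, or that poor uptake always improves the result. The documents do not support that: they give no event rates or session counts, and for engagement the direction depends on who declines.

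**What to change.** - **Tolerability:** in the criterion, count a participant as not tolerating if they withdraw, or decline a session, with pain or nausea as the recorded reason. Beside the 70% figure, report the number of sessions per participant and the per-session rate of rises of 3 or more with a participant-clustered 95% CI, by stage and setting. State whether between-session rises count.
- **Engagement:** average duration within participant first, then across participants. Report the share of offered sessions accepted as a separate figure. Scoring declined sessions as 0 minutes is not advised, because it turns a measure of engagement into one of adherence.
- **Not a short fixed window:** restricting tolerability to, say, the first three sessions would equalize exposure, but with one stage a day it cannot cover the five program stages and may precede home use.
- **Timing:** phase 4A is under way, so date the revised rule and report it beside the published one.

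The cost is a change of analysis wording and a little more analysis, since the NRS scores and the reasons are already recorded. The figures may be slightly less favorable.

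### A score starting at 8 to 10 cannot register the 3-point rise that the phase 4A tolerability criterion counts, so worsening from high starting scores is under-counted

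*Protocol article*

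**What the plan says.** Under Phase 4A, Data Analysis, the program is judged tolerable if "at least 70% of the participants do not report any pre- or post-NRS score increases of ≥3 for PLP, RLP, or nausea". This is one of the preset criteria that must be met.

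The measurements are described under Phase 3, VR Intervention Procedure. Before each session the research assistant gives "Numerical Rating Scales (NRSs; 11-point Likert scales) for PLP, residual limb pain" and nausea. After the session, "Afterward, the research assistant verbally readministered the NRSs for PLP, RLP, and nausea". The same section lets a participant move to the next stage only if "NRS scores did not increase by >2 points during or before their next session", and gives as the reason that "3 points is considered a clinically significant increase". It also has the research assistant record why a participant declined a session or stopped it before 20 minutes.

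Phase 4A takes these arrangements over: "Similar procedures to phase 3 will be used in phase 4A, with 3 exceptions". None of the listed exceptions alters the rating scales. On duration, "Participants will be allowed to continue the VR-GMI program for up to 17 days".

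Neither the criterion nor the progression rule makes any provision for high starting scores. The eligibility criteria under Recruitment in phases 3 and 4A set no upper limit on pain.

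**The concern.** Both rules count an absolute rise. Near the top of a bounded scale there is not enough room for that rise, so a worsening that the participant feels cannot appear as an event. It is then scored in the same way as a session in which nothing got worse.

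The protocol article gives reasons to think that high starting scores will occur. The Abstract and the Purpose and Rationale describe phantom limb pain as at its worst soon after amputation. The phase 1 partners reported that their pain was worst at onset. Residual limb pain, at a recent surgical site, is scored as well. The procedure itself allows that treatment may make pain or nausea worse.

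At stake is one of the criteria for taking the program forward to a randomized trial. With about 25 to 30 participants, a few unregistered worsenings could decide whether 70% is reached.

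**Working it through.** **Inputs.** The rise threshold (3 or more), the three scales and the 70% share come from Phase 4A, Data Analysis. The 11-point scale comes from Phase 3, VR Intervention Procedure. The sample of 30 recruited and 25 expected to complete comes from Phase 4A, Recruitment. The end points 0 and 10 are an assumption. On any 11-point scale with unit steps, the top three scores cannot rise by 3.

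**The plan's own figure.** The 70% is a set threshold with no calculation behind it, so there is nothing to reproduce. In whole participants it means 0.70 × 30 = 21 of 30, or 0.70 × 25 = 17.5, hence 18 of 25.

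**Step 1: the ceiling.** Largest possible rise = 10 − starting score.

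- Start 7: 3, so an event can register.
- Start 8: 2. Start 9: 1. Start 10: 0. No event can register on that scale in that session.

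On whole numbers a rise of more than 2 is a rise of 3 or more, so the progression rule has the same limit.

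**Step 2: how far one high score protects against failing.** A participant fails on any of three scales. There are 11³ = 1,331 combinations of starting scores for the three scales in one session.

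- At least one scale at 8 or more: 1,331 − 8³ = 1,331 − 512 = 819.
- All three at 8 or more: 3³ = 27.
- At least one high, but another scale still free to rise by 3: 819 − 27 = 792.

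These are counts of combinations, not frequencies in patients. They show that masking acts per scale and per session. A participant is certain to pass only if all three scales start at 8 or more in every session.

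**Step 3: illustration of size, with assumed inputs.** Let t be the share of participants who truly worsen by the criterion's standard, and c the share of those whose events meet the ceiling. The share counted as tolerating is

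- 1 − t(1 − c) if the masked events are lost altogether;
- 1 − t(1 − c/2) if half of them are caught on another scale or in another session.

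The chance of meeting the criterion is the binomial probability of at least 21 of 30, or at least 18 of 25. With t = 40%, for fully masked / half caught:

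| c | Share counted as tolerating | Chance, n = 30 | Chance, n = 25 |
|---|---|---|---|
| 0 | 60% | 17.6% | 15.4% |
| 10% | 64% / 62% | 31.6% / 24.0% | 27.1% / 20.7% |
| 20% | 68% / 64% | 49.4% / 31.6% | 42.5% / 27.1% |
| 30% | 72% / 66% | 68.1% / 40.1% | 60.0% / 34.4% |

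**Step 4: the upper bound.** Suppose a share f of participants passed automatically and the others had a true rate q. The reported rate would be f + (1 − f)q.

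- f = 20%, q = 65%: 0.20 + 0.80 × 0.65 = 72%.
- f = 30%, q = 60%: 0.30 + 0.70 × 0.60 = 72%.

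If the high scorers instead fail at half the ordinary rate, through other scales or sessions, the results are 0.20 × 0.825 + 0.80 × 0.65 = 68.5% and 0.30 × 0.80 + 0.70 × 0.60 = 66%. Both fall below 70%, so the 72% figures hold only under complete masking.

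**The case against.** A reader might infer that participants in the worst pain are counted as tolerating the program whatever happens. The documents do not support that. Someone with phantom pain at 9 still fails on a 3-point rise in residual limb pain or nausea, or in phantom pain in a session that starts at 7 or below. Sessions are daily for up to 17 days.

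Four further objections deserve weight.

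- **Frequency is unknown.** No starting scores are reported. Eligibility runs to 2 months after amputation, sessions continue at home, and the program is also aimed at people whose phantom pain has not begun. Scores are taken before participants are asked whether they want a session that day, so someone in severe pain can decline. This stands, and it is why no size can be claimed.
- **The net bias is not shown.** One 3-point rise on any of three scales over many sessions, without a control group, is easy to reach through ordinary postoperative fluctuation. That pushes towards failing. This stands too: what is shown is the direction of the ceiling effect alone.
- **Intolerance is visible elsewhere**, in the reasons for declining or stopping, the withdrawal data and the session-duration criterion. This is true, but none of it enters the tolerability rate.
- **The two rules agree with each other.** They do, on whole numbers. The difficulty lies between both rules and the range of the scale.

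**Conclusion.** The point holds in a limited form. Given an 11-point scale with unit steps (0 to 10 assumed), a 3-point worsening cannot register from a start of 8, 9 or 10 on that scale in that session. Neither rule allows for this. Taken alone, the effect can only raise the share reported as tolerating the program. It does not make any participant pass automatically, short of all three scales starting at 8 or more in every session.

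The size cannot be derived from the protocol article. The table shows that a modest amount of masking could matter at this sample size, but t and c are assumptions. The 72% examples are upper bounds and should not be read as the expected effect. Reading the loosely worded pre- or post-session increase as a change within or between sessions does not remove the ceiling.

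**What to change.** Keep the preset 70% criterion unchanged as the main result. Phase 4A is under way, with 15 participants recruited by March 2025, and a preset threshold should not be redefined in mid-study. Before the tolerability data are analysed, add two items under Phase 4A, Data Analysis:

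1. Report how many scores, counted per scale and per session, started at 8 or more. Report also how many participants counted as tolerating had at least one such score. This shows whether the ceiling is trivial or material.
2. Specify a supplementary tolerability rate in which a session stopped early for pain or nausea also counts as an event. Apply it to all participants whatever their starting score, so that there is one event definition. State whether the 70% conclusion holds under both rates.

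No new data are needed, because starting scores and reasons for stopping are already recorded. The cost is slightly more analysis and possibly a less favourable figure. The supplementary rate recovers only worsening that led to an early stop, so the counts in item 1 are still needed beside it.

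The sponsor should also reconcile the stage-progression rule under Phase 3, VR Intervention Procedure, which phase 4A takes over, with the range of the scale. No clinical rule is proposed here.
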